### Statistical analyses and power calculation

Baseline participant characteristics stratified by treatment group will be presented. Group differences will be tested using *t* tests for continuous variables and chi-square tests for categorical outcomes. Parametric test assumptions will be examined and reported. Non-parametric data will be transformed or alternatively analyzed using non-parametric statistical tests. Multiple imputation will be used to replace missing internal values where appropriate. Within-group changes in the primary outcome (alcohol consumption) and secondary outcomes (depression, anxiety, cognitive ability, etc.) will be analyzed using paired-sample *t* tests. To address the primary research question, intention-to-treat analyses will be performed. The effect of group allocation on alcohol consumption and all secondary outcomes at 3-month follow-up will be assessed using mixed linear regression models (logistic for binary outcomes), using both the mean difference (baseline to 3 months) and total scores as dependent variables. Where the total score is used as the outcome, baseline group differences in covariates will be adjusted. As adherence may be sub-optimal, per-protocol analyses will also be presented. Data from individual accelerometers will be pooled to objectively assess changes in physical activity levels before and after treatment. We propose to conduct sub-group analyses based on participant gender and age to assess the effects of these variables on alcohol consumption. All analyses will be performed using SPSS 22.0. All tests will be two-sided and *P* values of less than 0.05 considered statistically significant.

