Our sample size calculation is based on a preliminary study of the effects of exercise on alcohol consumption by Brown et al., 2015 [38]. Using this study as a guide, we anticipate a standardized mean difference (effect size) of around 0.3 favoring the yoga and aerobic exercise groups equally, compared to TAU. Our recent meta-analysis identified a pooled dropout rate of 40% from exercise for AUD studies. Due to the incentives in our trial, we estimate a slightly lower dropout of around 30%. Based on these parameters, with an 80% power, two-tailed significance of 2.5% to allow for two primary between-group comparisons (yoga versus TAU, and aerobic exercise versus TAU), and 1:1:1 allocation, we estimate that a total sample size of 210 participants will be required (i.e., 70 in each group). We used the program G*Power to determine sample sizes [39].

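### The stated decision rule (P<0.05 for all tests) conflicts with the two-sided 2.5% set for each of the two primary comparisons; applied as written, it gives a family-wise error of about 9.1% instead of about 4.6%

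*Protocol article*

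**What the plan says.** Both statements stand in the protocol article under the heading Statistical analyses and power calculation.

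- **Analysis paragraph.** After listing the baseline comparisons, within-group tests, between-group models, per-protocol analyses and subgroup analyses, it closes with one rule for everything: "All tests will be two-sided", with P "values of less than 0.05 considered statistically significant". It exempts nothing and states no adjustment, testing order or overall test that must be passed first.
- **Sample-size paragraph.** It takes a "two-tailed significance of 2.5% to allow for two primary between-group comparisons" and names them: "yoga versus TAU, and aerobic exercise versus TAU". The other inputs include "1:1:1 allocation".

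Two further statements determine how many primary tests there are. The section on baseline and follow-up assessments gives primary status to alcohol consumption measured by TLFB and lists AUDIT as a separate item, whereas the abstract names TLFB and AUDIT together. The analysis paragraph models alcohol consumption both as a change score and as a total score, without ranking the two.

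**The concern.** The 2.5% is 5% divided by two comparisons, which is a Bonferroni split. The authors recognised that either exercise arm could produce a positive primary result and allowed for it in the design. The only sentence that defines significance does not carry the split over. Its wording covers all tests, so it includes the two primary ones.

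What is at stake is how the main result is read. If yoga versus TAU gave P = 0.04, the analysis paragraph would call it significant, while the level set in the sample-size paragraph would not be met. With both levels in print, the choice could be made after the result is known, and a pre-specified rule is there to prevent that. If the 0.05 rule is simply followed, the protection that the sample-size paragraph allowed for is lost.

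**Working it through.** **Inputs.** From the analysis paragraph: two-sided tests at 0.05. From the sample-size paragraph: two comparisons against a common TAU arm, equal allocation, 0.025 two-sided per comparison. The calculation uses a normal approximation with equal variances under the null hypothesis of no difference between the three arms. Sample size, standard deviation and effect size do not enter.

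**The plan's own level.** 0.05 / 2 = 0.025 per comparison, and 2 × 0.025 = 0.05 is the Bonferroni bound. The stated 2.5% is therefore exactly what is needed to hold two comparisons at 5%.

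**Correlation of the two test statistics.** Each is (exercise mean − TAU mean) divided by its standard error. With equal arms, the covariance of the two differences is σ²/n (the TAU mean's variance) and each difference has variance 2σ²/n. The correlation is (σ²/n) / (2σ²/n) = 0.5.

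**Family-wise error, both directions.** P(at least one |Z| > c) = 2α − P(both |Z| > c), with Z bivariate normal and correlation 0.5.

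- α = 0.05, c = 1.960: 0.1000 − 0.0093 = 0.0907, or 9.1%.
- α = 0.025, c = 2.241: 0.0500 − 0.0035 = 0.0465, or about 4.6%.

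Simulation of three equal arms gave 9.0% to 9.1% and 4.6%. For reference, independent tests would give 1 − 0.95² = 9.75% and 1 − 0.975² = 4.94%.

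**False superiority claims only.** P(at least one Z > c) = α − P(both Z > c), where α/2 is the upper-tail area for each comparison.

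- α = 0.05: 0.0500 − 0.0046 = 0.0454, or 4.5%.
- α = 0.025: 0.0250 − 0.0018 = 0.0232, or 2.3%.

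On either count, the 0.05 rule roughly doubles the error: 9.07 / 4.65 = 1.95 and 4.54 / 2.32 = 1.96.

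**Dunnett.** Using the correlation of 0.5, the level per comparison that gives 5% overall is about 0.027, slightly more generous than 0.025.

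**The case against.** The strongest defence is that a specific statement overrides a general one. The 0.05 sentence is a general closing line for a long list of analyses, while the next paragraph names the two primary comparisons and gives 2.5% to allow for them. On that reading, 2.5% governs those two tests and 0.05 the rest. This is probably what the authors meant, and it is why the 9.1% must be stated conditionally. It does not remove the conflict: the general line says all tests, and the 2.5% appears only as an input to the sample size.

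A second defence is that the multiplicity procedure may be in a statistical analysis plan that is not shown. If a significant overall test of the three groups were required first, the error with no difference between any arms would be about 4%. No such step is stated, however, and the point is not that detail is missing: the article does state a threshold, and it disagrees with the article's own design.

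A third objection is that 9.1% counts errors in both directions, including exercise appearing worse than TAU. That is correct. For false superiority claims the figures are 4.5% and 2.3%, so the doubling remains but the level is about half.

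A reader might also infer a larger error, because the abstract names AUDIT beside TLFB. Four tests at 0.05 would give about 14% to 17% for assumed between-outcome correlations of 0.8 to 0.3. The documents give no such correlation, and the assessment section reserves primary status for TLFB. That range is therefore an illustration under an assumption and not part of this finding.

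**Conclusion.** Wrong as written. One section gives two thresholds for the same two tests, and the only one stated as a decision rule is the one without the adjustment. If it is followed, the two-sided family-wise error is about 9.1% instead of about 4.6%, and false superiority claims occur about 4.5% of the time instead of 2.3%.

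These figures assume one outcome and one analysis per comparison, equal arms, a shared TAU group and no overall test beforehand. Testing both the change score and the total score would raise them by an amount that depends on their correlation.

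The documents do not support saying that the trial has given up its multiplicity protection, or that its error is 9% without condition. They support saying that the rule is contradictory and that 9.1% follows from one of its two readings. Nor does the contradiction bear on the status of the secondary outcomes.

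**What to change.** Replace the blanket sentence in the analysis paragraph with wording such as: *Each of the two primary comparisons (yoga versus TAU, aerobic exercise versus TAU) will be tested at two-sided 0.025 and reported with a 97.5% confidence interval. The primary outcome is alcohol consumption by TLFB, analysed as [change from baseline / total score adjusted for baseline]. All other tests are two-sided at 0.05.* Holm or Dunnett over the two comparisons is equally valid if named in advance.

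One dependent variable has to be chosen. Otherwise there are still four primary tests, and 0.025 per test does not secure 5%. The abstract should be brought into line with the single primary outcome. The change should be made and dated before any between-group result is seen.

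**Cost.** A sentence or two of text and no new data. Under the 0.025 rule, a primary P value between 0.025 and 0.05 no longer counts as significant. Under Holm it still counts if the other comparison is below 0.025.

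Power per comparison is also lower than at 0.05. For the stated "standardized mean difference (effect size) of around 0.3", 70 per arm and an unadjusted two-sample t test, it is about 31% at 0.025 and 42% at 0.05. With 49 completers per arm (70 × 0.7) it is about 22% and 31%. Both levels fall well short of the planned 80%. That is a separate problem with the sample size, and relaxing the threshold would not solve it.

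### The two primary comparisons are planned at a flat 2.5% each but the only stated test threshold is 0.05; naming Holm would settle the rule and gain a little power at no cost in error control

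*Protocol article*

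**What the plan says.** Both statements stand in the protocol article under Statistical analyses and power calculation.

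- **Sample-size paragraph.** The trial is sized at a "two-tailed significance of 2.5% to allow for two primary between-group comparisons", namely "yoga versus TAU, and aerobic exercise versus TAU". The assumed effect is a "standardized mean difference (effect size) of around 0.3 favoring the yoga and aerobic exercise groups equally, compared to TAU". The other inputs are "with an 80% power", "1:1:1 allocation" and 30% dropout, and the result is "a total sample size of 210 participants will be required (i.e., 70 in each group".
- **Analysis paragraph.** All tests are two-sided and are called significant when P is below 0.05. The two primary comparisons are not excepted, the 2.5% is not carried forward, and no sequential or step-down rule is named.

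**The concern.** The article contains two candidate rules for the primary comparisons and does not say which one decides them. Read literally, the analysis paragraph tests each at 0.05 with no allowance for there being two. Read through the sample-size paragraph, each gets 2.5%, whatever happens to the other.

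The second reading controls the error but leaves power unused. Once one comparison has succeeded at 2.5%, only one null hypothesis remains, and it can be tested at 0.05 without breaching 5% overall. The article expects an effect "favoring the yoga and aerobic exercise groups equally, compared to TAU". When both arms work, the second test is often reached, so the unused alpha matters most there.

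At stake are the error rate behind any claim for yoga or aerobic exercise and a modest amount of power in a trial that has little to spare.

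**Working it through.** **Inputs from the article.** Standardized difference d = 0.3 for each exercise arm against TAU; 1:1:1 allocation; 70 per arm; 30% dropout. Completers per arm: 70 × 0.7 = 49.

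**The article's own figure.** With two-sided 2.5% and 80% power, n per arm = 2(2.241 + 0.842)² / 0.3² = 211.2, so 212. Allowing for dropout, 212 / 0.7 = 302.9, so 303 per arm and 909 in total. The stated 210 is not reproduced. The comparison below therefore uses the planned 49 completers, with 212 per arm as a reference.

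**Set-up.** Normal approximation, equal variances and equal numbers.

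- Each test statistic has mean d√(n/2) = 0.3 × √24.5 = 1.485.
- The TAU mean is shared, so the correlation between the two statistics is (1/n) / (2/n) = 0.5.
- Critical values are 2.241 (two-sided 2.5%) and 1.960 (two-sided 5%).

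**Family-wise error when neither arm works.**

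- 0.05 for each: 1 − P(|Z1| < 1.960 and |Z2| < 1.960) = 9.1%.
- Flat 2.5%: the same expression with 2.241 gives 4.65%.
- Holm: also 4.65%, because its first rejection needs the same event.

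If exactly one arm is ineffective, Holm never tests that arm at a level above 0.05, so its error cannot exceed 5%.

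**Power with d = 0.3 in both arms, 49 per arm.**

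- Flat, per comparison: the upper tail is Φ(1.485 − 2.241) = Φ(−0.756), and the other tail is negligible. Result 22.5%.
- Flat, at least one: 1 − P(|Z1| < 2.241 and |Z2| < 2.241) = 34.6%.
- Flat, both: 2 × 22.5% − 34.6% ≈ 10.3%.
- Holm, at least one: the same event as for the flat split, 34.6%.
- Holm, both: at least one |Z| above 2.241 and both above 1.960 = 15.9%.
- Holm, per comparison: (34.6% + 15.9%) / 2 ≈ 25.3%.

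Step-down Dunnett uses a first critical value of 2.212 (large-sample, correlation 0.5) and then 1.960.

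| d = 0.3 in both arms | Flat 2.5% | Holm | Step-down Dunnett |
|---|---|---|---|
| 49 per arm, per comparison | 22.5% | 25.3% | 26.0% |
| 49 per arm, both | 10.3% | 15.9% | 16.1% |
| 49 per arm, at least one | 34.6% | 34.6% | 35.8% |
| 212 per arm, per comparison | 80.2% | 84.7% | 85.0% |
| 212 per arm, both | 69.0% | 78.0% | 78.2% |
| Family-wise error, no effect | 4.65% | 4.65% | 5.0% |

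**Only one arm works (0.3 and 0), 212 per arm.** Power for the effective arm is 80.2%, 80.3% and 81.1%. There is no loss, and with Holm almost no gain.

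**Enrolment for 80% power per comparison.** Holm needs 189 evaluable per arm: 189 / 0.7 = 270, and 3 × 270 = 810, against 909 for the flat split and 210 planned.

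**The case against.** **The 2.5% is not a stated testing rule.** It appears only among the sample-size inputs. A reader might infer that the article commits to a flat split and forbids reusing alpha, but it says neither. Sizing at 2.5% is compatible with a later Holm test. This stands, and it is why the point begins with the missing decision rule.

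**Against the literal 0.05 rule, Holm costs power.** At 0.05 for each comparison and 49 per arm, power is about 32% per comparison, against 25.3% with Holm. This is also true. The difference is the price of bringing the family-wise error down from about 9.1%, and the article's own planning level shows that an allowance for two comparisons was intended.

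**Bonferroni is valid, and the algorithm could sit in an analysis plan.** The flat split is not an error, and an unseen plan may already name a procedure. But the article does fix a threshold for all tests, and that threshold does not match its planning level.

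**The gain is small.** At the planned size it is about 3 points per comparison. A reader might infer that step-down testing is more powerful in every respect. It is not: Holm leaves power for at least one success unchanged, and other sequential rules can lose. A fixed sequence that starts with an ineffective arm leaves 3.7% power for an effective second arm at 212 per arm.

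**Two comparisons may not be the whole family.** The Abstract names both TLFB and the Alcohol Use Disorders Identification Test as the primary outcome, and the analysis uses both change and total scores. Holm across two arms protects one designated outcome and model only. The fix is therefore tied to TLFB, which the section on baseline and follow-up assessments names as primary.

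**Conclusion.** The point holds as a cheap improvement together with a clarification. The planning level (2.5% each) and the only stated test threshold (0.05) do not match, and no rule links them. Of the two readings, 0.05 for each leaves the family-wise error at about 9.1%; 2.5% for each is valid but dominated by Holm.

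At 49 completers per arm and d = 0.3 in both arms, Holm adds 2.8 points per comparison (22.5% to 25.3%) and 5.6 points for both (10.3% to 15.9%), and nothing for at least one. Holm's error control and its dominance over the flat split need no assumption about the correlation. The power figures assume normal statistics, equal evaluable numbers and correlation 0.5.

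A reader might also infer that a better testing rule rescues the sample size. It does not: Holm would still need about 810 enrolled for 80% power per comparison at the stated effect and dropout.

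**What to change.** In the analysis paragraph, add one sentence as an exception to the general 0.05 threshold. It should say that the two primary comparisons, yoga against TAU and aerobic exercise against TAU, on the primary TLFB outcome are tested by Holm: the smaller P value must be below 0.025 and, only if it is, the other is tested at 0.05. Tie the sentence to one designated analysis of that outcome. Keep 2.5% in the sample-size paragraph, labelled as the conservative planning level.

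Holm also suits the article's allowance for transformed or non-parametric analyses, because it works from P values alone. Where a normal-theory model is used, step-down Dunnett is an option (26.0% per comparison, 35.8% for at least one). It should then use the actual degrees of freedom and arm sizes, since 2.212 is a large-sample value for equal arms.

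The change needs no data and no patients, and should be made before results are seen. Its cost is that simultaneous confidence intervals matching a step-down test are less simple than a pair of 97.5% intervals. The sample size needs its own correction.

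### The sample size of 210 does not follow from its own inputs: at a standardised difference of 0.3 it gives about 22% power per comparison (31% with no dropout), not 80%

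*Protocol article*

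**What the plan says.** The calculation is in the Protocol article, section Statistical analyses and power calculation. All of its inputs are printed:

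- Effect: "we anticipate a standardized mean difference (effect size) of around 0.3 favoring the yoga and aerobic exercise groups equally, compared to TAU".
- Error rates: "with an 80% power, two-tailed significance of 2.5% to allow for two primary between-group comparisons".
- Comparisons and allocation: "yoga versus TAU, and aerobic exercise versus TAU), and 1:1:1 allocation".
- Dropout: "we estimate a slightly lower dropout of around 30" per cent, against a pooled 40% in the authors' meta-analysis.
- Software: "We used the program G*Power to determine sample sizes". The test family is not named.

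The result, presented as following from these parameters, is "we estimate that a total sample size of 210 participants will be required (i.e., 70 in each group"). The calculation mentions no baseline to follow-up correlation, covariate adjustment or repeated-measures assumption.

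**The concern.** A standardised difference of 0.3 is small. At two-sided 2.5% with 80% power, a two-group comparison of that size usually needs a little over 200 per group before any allowance for dropout. The stated 70 per group, 49 after the assumed dropout, is far below that.

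This concerns the trial's two primary comparisons. If the printed 80% stands, a non-significant result invites the reading that exercise does no better than TAU, although the trial had a small chance of detecting the effect it was planned around. Conversely, if the true effect is near 0.3, estimates that reach significance will tend to be exaggerated.

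**Working it through.** **Inputs** (all from the power section): d = 0.3; two-sided α = 0.025 per comparison; power 0.80; equal arms; dropout 30%; 210 randomised, so 70 per arm and 70 × 0.7 = 49 evaluable.

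**1. Sample size from the stated inputs.** Normal approximation, per arm:

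n = 2(z₁₋α/₂ + z₁₋β)² / d² = 2(2.241 + 0.842)² / 0.09 = 211.2, so 212.

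The exact noncentral t calculation gives 213. Allowing for dropout, 213 / 0.7 = 304.3, so 305 per arm and 3 × 305 = 915 in total. The stated 210 is 23% of that (210 / 915).

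**2. Power at the stated size.** Normal approximation: power = Φ(d√(n/2) − 2.241).

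- n = 49: 0.3 × √24.5 = 1.485; Φ(−0.756) = 22.5%. Exact t: 21.9%.
- n = 70: 0.3 × √35 = 1.775; Φ(−0.467) = 32.0%. Exact t: 31.5%.

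**3. Difference detectable with 80% power** at two-sided 2.5% (exact t): 0.631 with 49 per arm and 0.526 with 70.

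**4. Looser readings, still at d = 0.3.**

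| Reading | 49 per arm | 70 per arm |
|---|---|---|
| Two-sided 2.5%, as stated | 22% | 31% |
| Two-sided 5% | 31% | 42% |
| One-sided 5% | 43% | 55% |
| Two-sided 2.5%, adjusted for baseline, r = 0.5 | 29% | 42% |
| Two-sided 2.5%, adjusted for baseline, r = 0.7 | 42% | 59% |
| Two-sided 2.5%, adjusted for baseline, r = 0.8 | 58% | 75% |

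Pooling both exercise arms against TAU (98 v 49, two-sided 2.5%) gives 29%. The adjusted rows use an effective difference of 0.3 / √(1 − r²); r is an assumption, since the document gives none. Setting 0.3 / √(1 − r²) equal to the detectable difference gives the r needed for 80%: √(1 − (0.3/0.631)²) = 0.88 with 49 per arm and √(1 − (0.3/0.526)²) = 0.82 with 70. Analysing change scores at 49 per arm gives 22% at r = 0.5 and 36% at r = 0.7.

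**5. Can 210 be reproduced?** Not by any two-group calculation tried on the stated inputs. One undeclared route comes very close: a three-group, two-time-point repeated-measures interaction F test.

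- Three means of 0.3, 0.3 and 0 have f = 0.3 × √(2/9) = 0.1414.
- With α = 0.025, r = 0.5 and N = 147, the noncentrality is 0.1414² × 147 × 2 / 0.5 = 11.76 and power is 79.9%; 147 / 0.7 = 210.

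That this was the route is only an inference. It would not justify the figure in any case. It is an omnibus test rather than the two stated comparisons, and it uses the f of the post-treatment means as if it were the interaction f. If the arms are equal at baseline, the interaction f is half as large, 0.0707. The noncentrality is then 2.94 and power 21.7%. Conversely, an interaction f of 0.1414 corresponds to a post-treatment difference of about 0.6, not 0.3.

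**The case against.** The arithmetic on the stated inputs is not in dispute. The best case for the plan is that 22% is its least favourable reading.

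- **Dropout need not mean a missing outcome.** The 40% that anchors the dropout assumption may refer to leaving the exercise programme. The section Follow-up assessments and qualitative study offers people who decline the week 13 visit a phone interview or a mailed form that includes the Timeline Follow-back. This stands, so the fair unadjusted range is 22% to 31%. Against it, the power section itself uses 30% for sizing, and the week 6 removals described in the same follow-up section could add losses.
- **The analysis may gain precision from baseline.** The plan analyses change and also adjusts total scores for baseline differences. With 70 per arm and r = 0.8, power would be about 75%. This narrows the gap, but it combines no loss at all with a high correlation that the document does not state.
- **The article may omit the G*Power routine.** A condensed article can leave that to the full protocol, so its absence is not itself an error. The error is that the printed inputs and the printed result disagree.
- **Restating the power does not make the trial adequate for 0.3.** This is fair: restating corrects the claim, and only a larger sample would restore 80% at that effect.

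**Conclusion.** The concern holds. On the protocol's own inputs the required total is about 915, not 210. The planned size gives about 22% power per comparison with 30% of outcomes missing and about 31% with none missing. The effect detectable with 80% power is 0.63 or 0.53 respectively, roughly twice the 0.3 assumed.

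The 22% and 31% are for unadjusted two-group comparisons of means at two-sided 2.5%. Baseline adjustment at assumed correlations of 0.5 to 0.7 raises them to 29–42% (49 per arm) or 42–59% (70 per arm), and 80% is reached only at about 0.88 or 0.82. No reading tested that keeps a true post-treatment difference of 0.3 reaches 80% without a correlation of that order. The conclusion does not depend on how 210 was obtained.

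**What to change.** Keep 210 and replace the power claim with what that number supports, for example:

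> With 70 randomised and about 49 evaluable per arm, each comparison with TAU has 80% power at two-sided 2.5% for a standardised difference of about 0.63 unadjusted, or 0.55 to 0.45 if baseline consumption is adjusted for and its correlation with follow-up is 0.5 to 0.7. Power for a difference of 0.3 is about 22% unadjusted and 29% to 42% adjusted.

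The adjusted values are 0.631 × √(1 − 0.5²) = 0.55 and 0.631 × √(1 − 0.7²) = 0.45. If dropout from exercise is expected to leave the primary outcome largely complete, say so and give the figures for 70 per arm as well: 0.53 unadjusted, and 0.526 × √(1 − 0.5²) = 0.46 to 0.526 × √(1 − 0.7²) = 0.38 adjusted.

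Name the G*Power routine with its effect-size definition and any correlation used. State whether an effect of that size is plausible. Add that a non-significant result will be reported through its confidence interval and not as absence of effect.

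This costs wording only and no extra participants, but the stated power becomes less favourable. The alternative, if 80% power at 0.3 is essential, is to revise the sample size, to about 915 for an unadjusted comparison with 30% loss.
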